**(v) Rationale for this study**

This study is preceded by two others: EV01 and EV02. In EV01 the safety and immunogenicity of NYVAC-C x 2 was assessed. EV02, which finished in 2006, provided additional safety data to EV01 on NYVAC-C, and the first immunogenicity data in humans on the use of DNA-C as a priming agent, comparing DNA-C x2 + NYVAC-C x2 to NYVAC-C x2 alone. The highest practicable dose of DNA-C was investigated in EV02 and a significantly higher proportion of volunteers that completed the prime-boost regimen had IFN $\gamma$  ELISpot responses compared to those that received both NYVACs, 90% compared to 40% (2-sided Fisher's exact Test:  $p = 0.003$ ).

During the implementation of EV02 a consensus began to emerge that three DNA immunisations may be required for optimal priming. Data from the exploratory DNA x3 prime – Ad5 x1 boost trial supporting this hypothesis were presented at the AIDS Vaccine Conference 2006 in Amsterdam, with higher mean responses and an increase in the breadth of response with most participants responding to gag as well as *env* [26].

This study proposes to compare the DNA-C x3 prime + NYVAC-C x1 boost to the DNA-C x2 prime + NYVAC-C x2 boost in a large enough study to make a robust assessment.

The design will be open to the participants and investigators, but the laboratory personnel conducting the ELISPOT, flow cytometry and antibody assessments will be blind to allocation. The randomisation will be stratified by gender to ensure an equal proportion of women in each group.

EuroVacc 03/ANRS Vacc 20 will address the following questions:

1. Does DNA-C x 3+NYVAC-C x1 elicit broader responses to peptide pools in IFN $\gamma$  ELISpot assays compared to DNA-C x 2+NYVAC-C x2?
2. Does DNA-C x 3+NYVAC-C x1 elicit higher mean responses across the peptide pools in IFN $\gamma$  ELISpot assays compared to DNA-C x 2+NYVAC-C x2?
3. Is DNA-C x 3+NYVAC-C x1 safe compared to DNA-C x 2+NYVAC-C x2?

## II Summary of Trial

140 healthy volunteers at low risk of HIV infection will be entered into the study to receive one of the following regimens:

|                                | Wk 0                                                       | Wk 4                                                       | Wk 8                                                       | Wk 20                                             | Wk 24                                             |
|--------------------------------|------------------------------------------------------------|------------------------------------------------------------|------------------------------------------------------------|---------------------------------------------------|---------------------------------------------------|
| group 1
"DNAx3"

n=70 | DNA-C
2x2ml IM
right and left
vastus
lateralis | DNA-C
2x2ml IM
right and left
vastus
lateralis | DNA-C
2x2ml IM
right and left
vastus
lateralis |                                                   | NYVAC-C
1 ml IM
Non-
dominant
deltoid |
| group 2
"DNAx2"

n=70 | DNA-C
2x2ml IM
right and left
vastus
lateralis | DNA-C
2x2ml IM
right and left
vastus
lateralis |                                                            | NYVAC-C
1 ml IM
non-
dominant
deltoid | NYVAC-C
1 ml IM
Non-
dominant
deltoid |

Participants will attend the clinical centre on at least 14 occasions over 72 weeks. These visits will comprise:

- Screening
- Enrolment, trial entry and first immunisation
- Second immunisation
- Third immunisation
- Fourth immunisation
- Early follow-up after each immunisation
- Two other follow-up for safety and immune responses
- Week 48 final safety visit
- Week 72 immune responses

### Procedures

Participants will have blood and urine collected, and receive the immunisations as outlined in the schedule (see 2.6). They will be counselled prior to and following a HIV test, and given health education on prevention of sexually transmitted infections including HIV.

### Endpoints

The primary end-points are:

- Immunogenicity: cellular responses to *env*, *gag*, *pol* and *nef* assessed using the IFN- $\gamma$  ELISPOT technique. The two treatment groups will be compared in terms of the proportion responding to *env* plus at least one of the *gag*, *pol*, *nef* peptide pools at weeks 26 or 28 using the Chi-square test.
- Safety: local (pain, cutaneous including induration), general (fever, chills, headache, nausea, vomiting, malaise, myalgia) and other unsolicited adverse events within 7 and 28 days.

### Institutional responsibility in trial

Product supply and indemnity for product:

- The EuroVacc Foundation will be responsible for the provision of indemnity for any claim by a clinical trial participant in respect of a SAE attributable to participation in the clinical trial, other than clinical negligence in the EuroVacc centres.

- The ANRS will be responsible for the provision of indemnity for any claim by a clinical trial participant in respect of a SAE attributable to participation in the clinical trial, in the ANRS Centres.
- The ANRS will act as the legal representative of Eurovacc foundation in the EU member states.
- Each clinical centre will hold indemnity for clinical negligence

Coordination of the data management and monitoring adherence to ICH GCP will be shared between the UK Medical Research Council Clinical Trials Unit (MRC CTU) and the INSERM U593 CTU, with responsibility for the EuroVacc centres and the ANRS centres respectively. The enrolment and serious adverse event reporting numbers are:

**EuroVacc centres - [contact] [contact]**  
**ANRS centres - [contact] [contact]**

An analysis plan will be developed by these two institutions in collaboration with all the participating investigators.

The EuroVacc trials are overseen by a Trial Coordinating Committee (TCC). The committee has an independent chair, [name], and two other independent members. The two Chief Investigators listed on this protocol will represent the EuroVacc/ANRS investigators and have voting rights on this committee. Additional non-voting members may attend as appropriate to the contents of the meeting. This committee will be responsible for final decisions about grade of adverse events and relationship to study vaccine, and will be determined by the evolution of the adverse event.

An entirely independent Data and Safety Monitoring Committee has been appointed to review the design and protocol, and will meet on one occasion during the trial, to review the safety data, after half the participants have completed the immunisation regimen and passed week 28. Using this dataset the investigators will review the pooled immunogenicity data blind to allocation and, if less than 60% of participants have ELISpot responses, then the DSMC will be asked to review the immunogenicity by allocation as well as the safety data, and make a recommendation based on the upper confidence bound of the difference between the two groups (DNAX3 – DNAX2). The members of this committee are:

|                         |                                          |
|-------------------------|------------------------------------------|
| [name]           | Chair and infectious diseases specialist |
| [name] [name]     | Clinical Epidemiologist                  |
| [name]      | Clinical Immunologist                    |
| [name] [name] | Biostatistician                          |

There will be an additional meeting if 3 or more participants experience an unexplained, unexpected grade 3 or 4 clinical or laboratory event (confirmed on attendance or repeat testing) not resolved within 72 hours and considered probably or possibly related to vaccine product.

Screening will not commence until the approvals appropriate to the clinical centre according to ICH GCP have been obtained.

**III Scientific questions to be addressed:**

| Regimen                    | Wk 0                                              | Wk 4                                              | Wk 8                                              | Wk 20                                      | Wk 24                                   |
|----------------------------|---------------------------------------------------|---------------------------------------------------|---------------------------------------------------|--------------------------------------------|-----------------------------------------|
| group 1
"DNAx3"
N=70 | DNA C 2x2ml IM right
and left vastus lateralis | DNA C 2x2ml IM right
and left vastus lateralis | DNA C 2x2ml IM right
and left vastus lateralis | Nothing                                    | NYVAC C 1 ml IM
Non-dominant deltoid |
| group 2
"DNAx2"
N=70 | DNA C 2x2ml IM right
and left vastus lateralis | DNA C 2x2ml IM right
and left vastus lateralis | Nothing                                           | NYVAC C 1 ml IM
Non-dominant
deltoid | NYVAC C 1 ml IM
Non-dominant deltoid |

| Primary Questions                                                                                                                                                   | Datasets                                                                                        | Primary safety and immunogenicity end-points                                                                                                                                                                                                              |
|---------------------------------------------------------------------------------------------------------------------------------------------------------------------|-------------------------------------------------------------------------------------------------|-----------------------------------------------------------------------------------------------------------------------------------------------------------------------------------------------------------------------------------------------------------|
| Is there a quantitative difference in the breadth of immune responses following the 3 prime regimen compared to the 2 prime regimen?                                | Wks 26, 28 IFN $\gamma$
ELISPOT
1 vs 2                                                    | The proportion of individuals in each group with CD8/CD4+ T cell responses to env plus at least one of the gag, pol, nef peptide pools                                                                                                                    |
| Secondary Questions
Is there a quantitative difference in the strength of immune responses following the 3 prime regimen compared to the 2 prime regimen? | Wks 26, 28 IFN $\gamma$
ELISPOT
1 vs 2                                                    | Mean IFN $\gamma$ ELISPOT response across peptide pools and wks 26 and 28 per group                                                                                                                                                                       |
| Is there a quantitative and/or qualitative difference in CD4 and CD8 T-cell responses following the 3 prime regimen compared to the 2 prime regimen?                | Wks 26, 28
Flow cytometry :
Intracellular
synthesis of IL-2/
IFN $\gamma$
1 vs 2 | Proportion of individuals in each group with CD4 and CD8 T cell responses to HIV peptide pools assessed by the percentage of cells producing IL-2 and/ IFN $\gamma$ . Comparisons between groups of mean percentages of HIV specific CD4 and CD8 T cells. |
| Is the 3 prime regimen safe compared to the 2 prime regimen?                                                                                                        | All weeks
1 vs 2                                                                             | Proportion of participants per group with grade 3 or above adverse events during the trial, excluding those considered unrelated to vaccine                                                                                                               |

**Detailed study schedule in section 2.6**

**1.0 General plan****1.1 Objectives**

The primary objectives are to compare the immunogenicity and safety of the three DNA-C prime and one NYVAC-C boost regimen to two DNA-C prime and two NYVAC-C boosts in healthy volunteers at low risk of HIV infection.

**1.2 Design and duration of the study****1.2.1 Design**

This is a randomised phase I/II international trial with a parallel group design, open to participants and investigators but blind to laboratory personnel.

**1.2.2 Start of enrolment and duration of the study**

The plan is to start the study in Q1 2007, with the aim to enrol within 9 months. The duration of the study per participant is 72 weeks. The duration of participation from screening to final visit is a maximum of 78 weeks per participant.

**1.3 Population**

The study will require 140 healthy male and female volunteers who are HIV negative and at low risk of HIV infection recruited through several clinical centres.

|                           |
|---------------------------|
| Inclusion Criteria |
|---------------------------|

- age between 18 and 55 years on the day of screening
- available for follow-up for the duration of the study (78 weeks from screening)
- able to give written informed consent
- at low risk of HIV and willing to remain so for the duration of the study
  - low risk of HIV infection defined as:**
    - no history of injecting drug use in the previous ten years
    - no gonorrhoea or syphilis in the last six months
    - no high risk partner (e.g. injecting drug use, HIV positive partner) either currently or within the past six months
    - no unprotected anal intercourse in the last six months, outside a relationship with a regular partner known to be HIV negative
    - no unprotected vaginal intercourse in the last six months outside a relationship with a regular known/presumed HIV negative partner
- willing to undergo a HIV test
- willing to undergo a genital infection screen
- if heterosexually active female, using an effective method of contraception with partner (combined oral contraceptive pill; injectable contraceptive; IUCD; consistent record with condoms if using these; physiological or anatomical sterility in self or partner) from 14 days prior to the first vaccination until 4 months after the last, and willing to undergo urine pregnancy tests prior to each vaccination
- if heterosexually active male, using an effective method of contraception with their partner from the first day of vaccination until 4 months after the last vaccination
- for French volunteers only :
  - subjects registered in French Health ministry computerised file and authorised to participate in a clinical trial
  - subjects covered by Health Insurance
  - subjects included in the ANRS vaccine research network of volunteers

|                           |
|---------------------------|
| Exclusion Criteria |
|---------------------------|

- pregnant or lactating
- clinically relevant abnormality on history or examination including history of grand-mal epilepsy; severe eczema; allergy to eggs or gentamicin; severe allergic diseases; liver disease with inadequate hepatic function; haematological, metabolic or gastrointestinal

disorders; uncontrolled infection; autoimmune disease, immunodeficiency or use of immunosuppressives in preceding 3 months

- receipt of live attenuated vaccine within 60 days or other vaccine within 14 days of enrolment
  - receipt of blood products or immunoglobulin within 4 months of screening
  - participation in another trial of a medicinal product, completed less than 30 days prior to enrolment
  - history of severe local or general reaction to vaccination defined as
    - local:** extensive, indurated redness and swelling involving most of the antero-lateral thigh or the major circumference of the arm, not resolving within 72 hours
    - general:** fever  $\geq 39.5^{\circ}\text{C}$  within 48 hours; anaphylaxis; bronchospasm; laryngeal oedema; collapse; convulsions or encephalopathy within 72 hours
  - HIV 1/2 positive or indeterminate on screening
  - positive for hepatitis B surface antigen, hepatitis C antibody or serology indicating active syphilis requiring treatment
  - positive for DNA/ANA antibodies at titre considered clinically relevant by immunology laboratory
  - grade 1 or above routine laboratory parameters (see section 4.1.4 & appendix 4 for definitions).
- Note of clarification 18th April 2008:* hyperbilirubinemia has to be considered as an exclusion criterion only when confirmed to be conjugated bilirubinemia.
- unlikely to comply with protocol

## 1.4 Trial products

### 1.4.1 Supply, storage and composition of NYVAC C

Transgene will be responsible for manufacture and supply of this clinical material according to Good Manufacturing Practice. The product is presented as a colourless solution at 1 mL per ampoule in single-use 2 mL glass ampoules and should be stored at  $-20^{\circ}\text{C}$  or below. The composition is given below:

| Name of Ingredient                | Concentration                   | Content/Ampoule |
|-----------------------------------|---------------------------------|-----------------|
| NYVAC-HIV (vP2010)                | $\geq 1.0 \times 10^7$ pfu / ml | $\geq 1.0$ ml   |
| Other Ingredients                 |                                 |                 |
| Tris Buffer                       | 1.21 g/L                        | 0.25 mL         |
| Lactoglutamate (Virus stabilizer) |                                 | 0.25 mL         |
| Freezing medium                   | According to formula 65-1-3     | 0.50 mL         |

### 1.4.2 Preparations prior to use of NYVAC C

Prior to use the ampoules will be thawed at room temperature for up to one hour. When completely thawed the ampoules should be gently swirled. Care must be taken not to shake or invert the ampoules.

### 1.4.3 Supply, storage and composition of DNA C

Cobra will be responsible for bulk manufacture of this clinical material, release testing and technical release of vialled product, and ProPharma for the preparation of the vialled material, including labelling. All procedures will be according to Good Manufacturing Practice. The presentation is in liquid form, with an extractable volume of 2ml to 2.2ml in 5ml vials which should be stored at  $-20^{\circ}\text{C}$  or below. The appearance is clear and the composition is given below:

| Name of ingredient   | Quantity per ml of DNA HIV-C vaccine |
|----------------------|--------------------------------------|
| DNA                  | 1.0 mg                               |
| Tris-HCl             | 1.57 mg                              |
| EDTA                 | 0.372 mg                             |
| NaCl                 | 9mg                                  |
| Water for injections | To 1 ml                              |

#### 1.4.4 Preparations prior to use of DNA C

Prior to use the vials will be thawed at room temperature. When completely thawed the vials should be gently swirled. Care must be taken not to shake or invert the vials.

#### 1.4.5 Labels

NYVAC C and DNA C will be packaged by Transgene and Cobra respectively. The trial products will be in ampoules or vials pre-labelled according to standardised operating procedures and statutory regulatory requirements.

Cartons will be supplied to the pharmacist responsible for each site for storing the used ampoules and vials labelled according to standardised operating procedures and statutory regulatory requirements.

#### 1.4.6 Dispensing records and disposal of unused product

The designated pharmacist will, upon receipt of supplies prior to commencement of the trial, conduct an inventory and complete a receipt, one copy of which will be retained at the site, one copy forwarded to MRC CTU (EuroVacc centres) or the INSERM U593 CTU (ANRS centres) and the original returned to the supplier. During the trial the pharmacist will be responsible for reviewing the dispensing log.

On the day of immunisation, and with the participant present, the Investigator will complete a prescription with the trial number, date of birth, and immunisation number (DNA 1, 2 or 3, NYVAC 1 or 2). The immunisation number and date will be entered against the trial number in the dispensing log. The ampoule/vial label will be cross-checked against the details on the prescription and dispensing log by two individuals, prior to product being administered.

The individual who administers the injection will be responsible for ensuring that the return of the used ampoules/vials is recorded in the dispensing log at the end of the clinical session, and that they are placed in the appropriate participant carton.

At the end of the trial all used and unused ampoules/vials will be checked against the inventory by staff from MRC CTU/INSERM U593 CTU before return to the supplier or disposal on site according to local pharmacy guidelines and applicable regulations. Documentation of disposal will be provided to the MRC CTU/INSERM U593 CTU, the Foundation and both suppliers.

During the trial, product accountability will be monitored by the prescriptions, the dispensing log, the returns, the trial register and data collected on the case report forms.

## 1.5 End-points

### 1.5.1 Primary

The primary endpoints are immunogenicity and safety as defined below.

The primary immunogenicity parameter will be the presence of CD8/CD4+ T cell responses defined according to internationally agreed criteria for evaluation of IFN $\gamma$  ELISPOT assays (see section 8),

- in response to *env plus* at least one of the *gag, pol, nef* peptide pools
- at weeks 26 or 28

The primary safety parameters will be graded according to appendix 4, and are:

- Grade 3 or above local adverse event (pain, cutaneous reactions including induration)
- Grade 3 or above systemic adverse event (temperature, chills, headache, nausea, vomiting, malaise, and myalgia)
- Grade 3 or above other clinical or laboratory adverse event confirmed at examination or on repeat testing respectively.
- Any event attributable to vaccine leading to discontinuation of the immunisation regimen.

Note of clarification 8th Nov 2006: This will capture all Serious Adverse Events (SAE) as defined by ICH GCP as well as other grade 3 and 4 events that do not meet the criteria of an ICH GCP SAE.

Data on local and systemic events listed above will be solicited with specific questions or using a diary card for a minimum of 7 days following each immunisation. Data on other clinical events and laboratory events will be collected with an open question at each visit and through routine scheduled investigations respectively.

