**2.3.2 Follow-up in the days following immunisation**

A diary card will be given, with instructions and a full verbal explanation, for participants to record local and systemic adverse events for at least 7 days following immunisation, as well as medication taken.

Participants will be observed on the day of immunisation as above. Contact will be maintained by the clinical team, using a method chosen by the participant, as indicated by the evolution of adverse events, up to resolution of solicited local and systemic events. Additional visits may be recommended at the discretion of the clinical and principal investigators, if clinically indicated or in order to clarify observations.

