#### 5.1.1 Serious Adverse Events (SAEs)

An adverse event is considered to be a “serious adverse event” by ICH Good Clinical Practice (ICH GCP) criteria if it results in the following:

- death,
- a threat to life,
- requires in-patient hospitalisation or prolongs existing hospitalisation (hospitalisation for elective treatment of a pre-existing condition is not included),
- results in persistent or significant disability or incapacity,
- is a congenital anomaly (ie, the outcome of pregnancy involving a participant), or
- is any other important medical condition\*.

\*Examples of conditions regarded as “any other important medical condition” include allergic bronchospasm requiring intensive emergency treatment, seizures or blood dyscrasias which did not result in hospitalisation or development of drug dependency.

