### 8.2 Primary analysis

The immunological end-points will be considered present or absent according to standardised operating procedures which take the background activity into account ( $> 4$ -fold the negative control and  $> 55$  Spot forming units/ $10^6$  cells). In both EV01 and EV02, a small proportion ( $<5\%$ ) of subjects showed persistent IFN $\gamma$  ELISpot reactivity to peptide pools prior to vaccination and subsequently across several timepoints. Subjects with IFN $\gamma$  ELISpot reactivity to peptide pools prior to vaccination will be considered to have non-specific cross-reactive responses to the peptide pools, and will be excluded from the immunogenicity analysis. The two groups DNAX2 and DNAX3 will be compared in terms of the proportion responding to *env* plus *gag/pol/nef* using a Chi-square test.

All safety end-points will be graded by the Clinical Investigators and reviewed by the Operational Sub-Group. Any queries about grade and relationship to study product that cannot be resolved will be referred to the Trial Coordinating Committee for a final decision. For the primary analysis of safety endpoints (as defined in section 1.5.1), results will be expressed as a proportion and the two groups compared using Fisher's exact test.

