| PULMONARY               |                                                                                                                                            |                                                                                            |                                                                                                               |                                                                                                                    |
| Cough (for aerosol studies)           | Transient; no R x                                                                                                               | Treatment associated cough; inhaled bronchodilator                                         | Uncontrolled cough; systemic R x req                                                               | -----                                                                                                              |
| Bronchospasm Acute                    | Transient; no R x ; FEV1 or peak flow reduced to 70% - 80%                                                                      | R x req; normalizes with bronchodilator; FEV1 or peak flow 50% - 69%            | No normalization with bronchodilator; FEV1 or peak flow 25% - 49%, retractions                                | Cyanosis; FEV1 or peak flow <25% OR intubated                                                                      |
| Dyspnoea                              | Dyspnoea on exertion                                                                                                                       | Dyspnoea with normal activity                                                              | Dyspnoea at rest                                                                                              | Dyspnoea requiring O 2 therapy                                                                          |

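### The note in section 1.5.1 says the primary safety parameters capture every SAE, but none of the four listed parameters is seriousness, so an SAE graded below 3 can fall outside them

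*Protocol*

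**What the plan says.** Protocol section 1.5.1 lists four primary safety parameters:

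1. local events of grade 3 or above;
2. systemic events of grade 3 or above;
3. a parameter for everything else: "Grade 3 or above other clinical or laboratory adverse event confirmed at examination or on repeat testing respectively";
4. events attributable to vaccine that lead to discontinuation of the regimen.

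The clarification of 8 November 2006 beneath the list says: "This will capture all Serious Adverse Events (SAE) as defined by ICH GCP as well as other grade 3 and 4 events".

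Section 5.1.1 defines an SAE by outcome. Its examples of other important medical conditions include "allergic bronchospasm requiring intensive emergency treatment, seizures or blood dyscrasias which did not result in hospitalisation". Section 8.2 ties the test to the list: "For the primary analysis of safety endpoints (as defined in section 1.5.1), results will be expressed as a proportion", with the groups compared by Fisher's exact test.

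**The concern.** The note states a property of the endpoint that the list does not have. Seriousness is not one of the four conditions, and grade and seriousness are separate scales. Section 5.1 says that some grade 3-4 events will be serious. It does not say that every SAE is grade 3 or 4.

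The composition of the primary safety proportion is at stake. A statistician who programs the four parameters gets one count, and one who programs the note can get another. A reader of the trial report who relies on the note would believe that every SAE is in the Fisher comparison when some may not be.

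**Working it through.** The protocol gives no safety rate, power or sample size, so there is no figure to reproduce. The check is logical.

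**The rule as listed.** An event counts if

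- (a) it is a local or systemic event of grade 3 or above; or
- (b) it is another clinical or laboratory event of grade 3 or above and is confirmed; or
- (c) it is attributable to vaccine and leads to discontinuation.

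**The property claimed.** Every SAE counts. One SAE that meets none of (a) to (c) disproves it.

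**SAE criteria in section 5.1.1 against the grades in Appendix 4.**

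| SAE criterion | Appendix 4 | Grade 3 or above assured? |
|---|---|---|
| Threat to life, event not in the tables | general scale: grade 4 | yes |
| Hospitalisation, event not in the tables | general scale: grade 4 | yes |
| Hospitalisation, row names it (e.g. myalgia, malaise, injection-site pain) | grade 4 | yes |
| Hospitalisation, row does not name it (diarrhoea) | 5-10 loose stools a day is grade 2 | no |
| Important medical condition: bronchospasm | treated case, "normalizes with bronchodilator; FEV1 or peak flow 50% - 69" per cent: grade 2 | no |
| Congenital anomaly | no row; general scale is framed by intervention and daily activity | no |

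The diarrhoea case matters because the general scale, which makes hospitalisation grade 4, applies only to events that the tables do not specify. Diarrhoea is specified, and no grade in its row mentions admission.

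**The remaining route, (c).** An SAE in a row marked no is certain to count only if it is attributed to vaccine and ends the schedule. Both groups receive their last dose at week 24, and the schedule in section 2.6 continues adverse event assessment to week 48. For 48 - 24 = 24 weeks there is no further immunisation to discontinue, so (c) cannot bring in an SAE that arises then.

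**The other half of the note.** Condition (b) requires confirmation, so an unconfirmed unsolicited grade 3-4 event does not count either, although the note carries no such limit. Condition (a) requires no confirmation, so solicited local and systemic events of grade 3 or above are unaffected.

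**Size.** Section 8.1 plans 70 per group. A participant whose only qualifying event is an omitted SAE changes that group's proportion by 1/70 = 0.014, or 1.4 percentage points. A participant already counted through another parameter changes nothing. The protocol gives no expected number of such SAEs. Its introduction reports no SAE and no grade 3 event in EV01, which recruited 24 volunteers. That suggests a small number but does not measure it.

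**The case against.** The strongest reply is that the note belongs to the endpoint section and can itself be read as bringing all SAEs in. That is a fair reading of the intent. It shows that list and note disagree, and it does not settle which governs when the data are counted.

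Several parts of the protocol also narrow the gap:

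- Section 5.4.1 rules out further immunisation after bronchospasm or convulsions within 72 hours. If attributed to vaccine with a dose still due, these enter through the fourth parameter at any grade.
- The vaccine-reaction table in Appendix 4 grades asthma within 6 hours of injection as severe even when admission is not needed, so an immediate reaction of that kind already counts.
- The example in 5.1.1 is allergic bronchospasm needing intensive emergency treatment, which may often be graded above 2.

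These points stand and reduce the number of cases. They do not cover later events, unattributed events, an admitted diarrhoea case or a congenital anomaly.

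A reader might infer more than the documents support in three ways:

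- *That the worst events are lost.* Hospitalised or life-threatening events are mostly grade 4, so the SAEs missed on grade are mainly those of lower severity.
- *That a severe unsolicited event is lost if it ends before a scheduled visit.* Section 1.5.1 does not say that confirmation means still present at a scheduled visit. Section 2.3.2 provides for extra attendance: "Additional visits may be recommended at the discretion of the clinical and principal investigators". The diary card asks participants to contact staff about grade 3 or 4 symptoms.
- *That the comparison is biased between groups because the first visit falls later after NYVAC-C than after DNA-C.* This needs short, early, unsolicited events, no unscheduled attendance, and nominal visit days despite windows of one week either side. Under other plausible onset times and durations it vanishes or reverses.

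**Conclusion.** The concern holds as an inconsistency in the definition of the primary safety endpoint. The statement that all SAEs are captured does not follow from the four parameters, and the literal rule can leave some SAEs out of the Fisher comparison. This rests on reading the list, to which section 8.2 points, as the operative rule.

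The practical effect is probably small and cannot be quantified from the protocol. Nothing disappears from reporting: section 1.5.2 keeps grade 1-2 events and all events as secondary endpoints, and section 8.3.2 puts all clinical events into the safety analysis. The correction is still worth making because it concerns a stated property of a primary endpoint and is simple.

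**What to change.** Add a fifth primary safety parameter to section 1.5.1: *any SAE as defined in 5.1.1, whatever its Appendix 4 grade*. The first half of the note is then true.

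Limit the second half to say that other, non-serious unsolicited clinical and laboratory events of grade 3 or 4 count when confirmed as the third parameter requires. Keep the confirmation condition. Participants and investigators know the allocation, so replacing confirmation with history or self-report would be a trade-off and not a plain improvement.

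The cost is wording only. Section 5.3 already has SAEs recorded and reported, so no new data, visits or participants are needed, and the test in section 8.2 is unchanged.
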